# Tranexamic Acid in Reducing Gross Hemorrhage and Transfusions of Spine Surgeries (TARGETS): study protocol for a prospective, randomized, double-blind, non-inferiority trial

**DOI:** 10.1186/s13063-019-3231-9

**Published:** 2019-02-12

**Keywords:** Topical, Intravenous, Tranexamic acid, Spinal fusion, Blood loss, Non-inferiority trial

## Abstract

**Background:**

Tranexamic acid (TXA) has been routinely delivered in multisegmental spinal decompression and bone graft fusion surgeries with satisfactory outcomes in minimizing gross blood loss and transfusion demands. However, concerns remain that intravenously delivered TXA (ivTXA) may increase risks of postoperative convulsive seizures and systemic thrombogenicity. Topical use of TXA (tTXA), being more targeted to the surgical bleeding site while minimizing patient systemic exposure to ivTXA, has been successfully applied to attenuate blood losses and transfusion requirements in hip and knee arthroplasty. Yet, randomized controlled trials on tTXA efficacy and safety are still lacking in spinal surgeries. With this knowledge gap, we hypothesize that tTXA exhibits non-inferiority to ivTXA in blood conservation and clinical safety in multisegmental spinal decompression and bone graft fusion surgeries.

**Methods:**

A prospective, randomized, double-blind, non-inferiority study design will be adopted. The target sample size is 176. Eligible patients will be randomly allocated to receive either ivTXA or tTXA treatment. The primary end point is the perioperative total blood loss. Secondary end points consist of visible blood losses (intraoperative, postoperative 0–24 h, postoperative 0–48 h, combined perioperative blood loss, total postoperative blood loss), postoperative hidden blood loss, plasma TXA levels, postoperative conventional coagulation monitoring (prothrombin time, activated partial thromboplastin time, fiber Bragg grating, international normalized ratio), postoperative thromboelastography monitoring (reaction time, clot formation time, clot strength, fibrinolysis), postoperative hemoglobin nadir (within postoperative 48 h), perioperative transfusion amounts and rates, and length of hospital stay. Safety end points will be monitored too.

**Discussion:**

This proposed study will contribute to expanding clinical evidences of tTXA for bleeding management in major spinal surgeries. This will be a high-quality prospective randomized trial with sufficient sample size, strict methodology, and few design deficits. It will investigate the potentiality of tTXA as an alternative to ivTXA in improving the current standard of care in multisegmental spinal surgeries, thereby optimizing the enhanced recovery after surgery scheme in spinal surgeries.

**Trial registration:**

ClinicalTrials.gov, NCT03011866. Registered on 5 January 2017.

**Electronic supplementary material:**

The online version of this article (10.1186/s13063-019-3231-9) contains supplementary material, which is available to authorized users.

## Background

Intravenously delivered tranexamic acid (ivTXA) has achieved satisfactory outcomes in minimizing gross blood loss and transfusion demands in complex surgeries [1–3]. However, in recent years, accumulating evidences have questioned the safety of ivTXA, as the treatment has been reported to cause postoperative seizures and systemic thrombogenicity [4, 5]. A 4.1-fold increase of postoperative seizures has been revealed as associated with ivTXA in adult cardiac surgeries [6], with the incidence increasing with larger ivTXA dosages [7, 8]. Additionally, the incidence rate of postoperative thromboembolic events reached 3% after high-dose ivTXA during spinal fusion surgery [9] and 1.7% in cardiac surgeries [4]. Furthermore, ivTXA dose ≥100 mg/kg, age over 75 years, and preoperative renal dysfunction have been identified as risk factors for developing postoperative TXA-related seizures and strokes [10, 11].

As a potential alternative of ivTXA, topical use of tranexamic acid (tTXA) targets concentratively at the surgical bleeding site while minimizing patient systemic exposure to ivTXA. tTXA treatment has been successfully applied to attenuate blood losses and transfusion requirements in hip and knee arthroplasty [12–14]. In spinal surgeries, though, randomized controlled trials (RCTs) on tTXA efficacy and safety are still lacking. With this knowledge gap, we hypothesize that tTXA exhibits non-inferiority to ivTXA in both blood conservation and clinical safety in multisegmental spinal decompression and bone graft fusion surgeries*.* To investigate the research question, a prospective, randomized, double-blind, non-inferiority study design will be adopted.

## Methods/design

### Hypotheses

To investigate the non-inferiority of tTXA to ivTXA in blood conservation and clinical safety, our working hypothesis is that tTXA-treated participants suffer *no more* blood losses or allogeneic transfusions, exhibit *undiminished* postoperative hemoglobin level and coagulation function, and are subject to *no increase* in length of hospital stay (LOH) and adverse event (AE) rate compared with those treated with ivTXA.

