### Sample size and statistical analysis

Our pilot cohort study indicated expected TBLs of 971 ± 459 ml and 911 ± 460 ml respectively in the tTXA and ivTXA groups in lumbar spinal decompression and 3–5 levels of bone graft fusion surgeries. Using PASS version 11.0, a sample size of 70 in each group is calculated to be sufficient with assumed type I error rate α = 0.05, power of test 1 – ß = 0.90, and 20% of TBL (195 ml) set as the non-inferiority cut off. Taking into account a dropout rate of 20%, a sample size of 88 in each group is eventually determined.

All the randomized participants who signed the Informed Consent Form (ICF) and satisfied all inclusion/exclusion criteria and have completed demographic data will be included in the intention to treat (ITT) analysis set. All the participants in the ITT set who have completed the perioperative TBL will be included in the per protocol (PP) analysis set. All the randomized participants who have received at least one dose will be included in the safety analysis (SS) set. All the analyses on efficacy will be based on the ITT set. Analysis on AEs will be based on the SS set.

For the primary outcome TBL, statistical methods for continuous variable analysis will be used in the non-inferiority test in the ITT analysis set, and a sensitivity analysis will be conducted in the PP set. The missing data will be treated as missing at random, and the multiple imputation procedure will be used for the primary outcome. The difference between the tTXA group and ivTXA group will be reported as mean difference and lower one-sided 95% confidence interval (CI), along with a one-sided *p* < 0.025.

For other outcomes, the Kolmogorov-Smirnov statistic with a Lilliefors significance level will be used for testing normality for continuous variables. Continuous variables with normal distribution will be compared using the Student *t* test between groups. The continuous parameters with a skewed distribution will be tested with the non-parametric Mann-Whitney *U* test between groups. The categorical variables will be presented as frequencies and percentages and compared using the chi-square test or Fisher’s exact test. If the total number of cases is less than 40 or the minimum expected count is less than 5, Fisher’s exact test will be used.

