For safety analysis, the AEs and abnormal findings in laboratory tests will be listed with the relationship to the study treatments. Fisher’s exact test will be used to compare the rates of participants who have at least one AE between groups in the SS set.

Statistical analyses will be performed using SPSS version 23.0 software (SPSS Inc., Chicago, IL, USA). A two-sided *p* < 0.05 is considered significant.

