While visible blood losses are well recognized and researched, the invisible HBL is relatively overlooked, largely due to its residual in dead spaces and extravasation into tissues. However, according to previous studies, both ours and others’, quantities of HBL in spine surgeries are substantial. Smorgick et al. reported that HBL accounted for 39–42% of TBL in primary/revision posterior spinal fusion surgeries [30], and a retrospective study conducted at our center reported the percentage as high as 47% [19, 31]. HBL has been reported as significantly associated with increased postoperative complications and LOH [32]; therefore, it constitutes a crucial component of the enhanced recovery after surgery (ERAS) scheme. Since there has been no study investigating the effect of tTXA on HBL, the issue will be investigated for the first time in this TARGETS study, with the hope that the study results will provide solid evidence for constructing the ERAS scheme in the spinal surgery field.

In the present study, thromboelastography (TEG) will be adopted for real-time evaluation of the coagulation system. By utilizing this dynamic functional hemostatic test, alterations in R time, K time, MA, and LY30 during the coagulation and lytic phases can be identified with minimal delay [33]. Combining the point-of-care (POC) TEG results and the systemic TXA levels revealed by the SPME technique [18], the potential rationale of tTXA on perioperative coagulation function will be precisely depicted, thereby attesting to the hemostatic efficacy as well as the safety profile of tTXA.

The strength of this study is that, for the first time, a prospective, randomized, double-blind, head-to-head study design with sufficient sample size will be adopted to investigate the clinical non-inferiority of tTXA to ivTXA in multisegmental spinal decompression and bone graft fusion surgeries. The results of this study will provide high-quality clinical evidence for the hemostatic efficacy and safety of tTXA application, thereby optimizing the TXA delivery route and the ERAS scheme in spinal surgeries.

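### Non-inferiority is hypothesized for safety and all secondary clinical outcomes, but only total blood loss has a margin and a non-inferiority test; equality tests on the rest cannot support that hypothesis

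*Protocol article*

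**What the plan says.** **Aim.** The Background states that "we hypothesize that tTXA exhibits non-inferiority to ivTXA in both blood conservation and clinical safety". The Hypotheses section repeats the aim ("To investigate the non-inferiority of tTXA to ivTXA in blood conservation and clinical safety") and turns it into a working hypothesis for each domain. Patients given tTXA should not have greater blood losses or more allogeneic transfusion, should have no worse "postoperative hemoglobin level and coagulation function, and are subject to" no rise "in length of hospital stay (LOH) and adverse event (AE) rate compared with those treated with ivTXA". The Discussion then promises that "The results of this study will provide high-quality clinical evidence for the hemostatic efficacy and safety of tTXA application".

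**Analysis.** The section on sample size and statistical analysis gives a single margin, "20% of TBL (195 ml) set as the non-inferiority cut off", and limits the non-inferiority test to the primary outcome, TBL. For the other outcomes it names between-group tests:
- "Continuous variables with normal distribution will be compared using the Student" t test;
- Mann-Whitney U for skewed variables;
- chi-square or Fisher's exact test for categorical variables.

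For AEs, Fisher's exact test "will be used to compare the rates of participants who have at least one AE between groups in the SS set". The section closes with a two-sided 0.05 significance criterion. TBL is the only outcome for which a confidence interval is mentioned.

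**The concern.** A t, Mann-Whitney, chi-square or Fisher test takes equality as its null hypothesis. A non-inferiority hypothesis takes as its null that the new treatment is worse by at least a stated margin. Failing to reject equality says nothing about whether an excess of that size has been excluded; it may only mean that the trial is small for that outcome.

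The hypotheses for AE rate, visible and hidden blood loss, transfusion, hemoglobin, coagulation and LOH are non-inferiority statements, and the named tests do not address them. Concern about the safety of ivTXA is the stated motivation for the topical route, and transfusion is in the trial's title. A statement that tTXA is no worse on these outcomes would therefore be prominent in the report, with nothing in the plan able to support it.

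**Working it through.** **1. Hypotheses against tests**

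| Outcome | Hypothesis for tTXA | Margin | Planned test |
|---|---|---|---|
| TBL | not worse | 195 ml | non-inferiority test |
| Visible and hidden blood loss | not worse | none | t or Mann-Whitney |
| Transfusion amount | not worse | none | t or Mann-Whitney |
| Transfusion rate | not worse | none | chi-square or Fisher |
| Hemoglobin, coagulation | not worse | none | t or Mann-Whitney |
| LOH | not worse | none | t or Mann-Whitney |
| AE rate | not worse | none | Fisher |

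Only the first row has a test that matches its hypothesis.

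**2. Arm size.** The plan's 88 per group follows from its 70 evaluable and 20% dropout: 70/(1 - 0.20) = 87.5, rounded up to 88. I use 88 throughout. This favours the plan, because fewer evaluable participants would lower every power figure below.

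**3. What the AE test could detect.** The document gives no expected rate of participants with at least one AE, so the rates here are assumptions shown as a range. The 3% borrows the Background's thromboembolic rate after high-dose ivTXA in spinal fusion, which is a narrower event than any AE; 10% has no source in the document.

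Exact power is the sum, over all counts i and j from 0 to 88, of P(X=i)·P(Y=j) for the pairs with two-sided Fisher p<0.05, where X ~ Bin(88, tTXA rate) and Y ~ Bin(88, ivTXA rate).

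| tTXA vs ivTXA rate | Power | Chance of p≥0.05 |
|---|---|---|
| 6% vs 3% | 7% | 93% |
| 20% vs 10% | 39% | 61% |
| 25% vs 10% | 70% | 30% |
| 30% vs 10% | 90% | 10% |

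A doubling from either base rate would usually be non-significant. A tripling from 10% would usually be found.

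**4. What a non-significant result leaves open.** Suppose 15/88 (17.0%) versus 8/88 (9.1%) have an AE. Fisher's two-sided p is 0.18. The difference is 7.95 percentage points. The Wilson limits are 10.6% to 26.2% and 4.7% to 16.9%. Newcombe's interval is then:
- lower: 0.0795 - √[(0.1705 - 0.1061)² + (0.1693 - 0.0909)²] = 0.0795 - 0.1014 = -0.022;
- upper: 0.0795 + √[(0.2624 - 0.1705)² + (0.0909 - 0.0468)²] = 0.0795 + 0.1020 = +0.182.

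So p=0.18 is compatible with an excess of up to about 18 points.

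**5. The same with equal observed rates.** The upper limit of the two-sided 95% interval for the excess is about 1.96·√[2p(1 - p)/88]. That is 5 points at p = 3%, 9 at 10% and 12 at 20%. Whether limits of this size support a claim depends on a margin, and the plan has none for AEs.

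**6. Continuous outcomes.** At 88 per arm, a two-sided 0.05 comparison of means has about 26% power for a true worsening of 0.2 SD and 51% for 0.3 SD. The problem is not confined to AEs.

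**The case against.** The strongest reply is that the faulty inference is never written down. A reader might infer that the plan will declare tTXA non-inferior in safety whenever p exceeds 0.05. The document does not state such a rule. The Objectives section speaks only of comparing the groups, and the analysis section keeps the margin for the primary outcome. One margin for the primary outcome with ordinary comparisons for secondary outcomes is a common layout. This stands, and it limits the point to a mismatch between hypothesis and analysis. It does not remove the mismatch: the Objectives section ties its comparisons to the preceding hypothesis, and no other criterion is given.

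A reader might also infer that the AE test would come out non-significant however much worse tTXA was. That is not so: power is 70% for 25% versus 10% and 90% for 30% versus 10%. The weakness concerns modest excesses and rare events.

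Third, tTXA is expected to be safer through lower systemic exposure, and a two-sided difference test is reasonable for showing that. This is fair as far as it goes. A significant result in favour of tTXA would support the hypothesis. A null result would not, and non-inferiority is what the document hypothesizes.

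Last, confidence intervals for secondary outcomes are often left to a full protocol or analysis plan, and their absence from an article is not an error. I agree. The point rests on what the article itself fixes: the hypotheses, the named tests and the significance criterion.

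**Conclusion.** The point holds as a mismatch within the document. Non-inferiority is hypothesized for AE rate, visible and hidden blood loss, transfusion, hemoglobin, coagulation and LOH, and the tests fixed for them cannot establish it. No passage reconciles the two. That conclusion needs no assumed rates; it follows from setting the hypotheses beside the tests.

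The size of the problem does rest on assumptions: 88 evaluable per arm and illustrative AE rates. On those, a true doubling would be missed about 61% of the time from a 10% base and about 93% from a 3% base.

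The primary analysis of TBL is not touched by this point. The change should be made, but this does not by itself undermine the trial's main comparison.

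**What to change.** Choose one of two routes for each outcome other than TBL, before data are analysed.

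1. **Narrow the claim.** Limit the confirmatory non-inferiority hypothesis to TBL in the Background, Hypotheses and Discussion, with the abstract aligned. Report AE rate, visible and hidden blood loss, transfusion amount and rate, hemoglobin nadir, coagulation indices and LOH as between-group differences with two-sided 95% CIs. State that p>0.05 will not be taken as non-inferiority.
2. **Or set a margin now.** For any outcome the sponsor wants to claim, specify and justify a margin and judge it on the confidence bound. The arm size limits what is feasible. With equal true AE rates, one-sided 0.025 and 90% power, n per arm = 2p(1 - p)(1.960 + 1.282)²/margin². For an illustrative 10-point margin this gives 62 at a 3% rate, 190 at 10% and 337 at 20%. With 88 per arm, such a claim is realistic only if AEs are rare or the margin is wide.

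The first route costs only wording and intervals from data already being collected, with no added participants or visits. Its downside is a narrower claim.

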### Objectives

With the preceding research hypothesis, the objectives of this study are to compare the perioperative visible/hidden blood losses, transfusion amounts/rates, plasma TXA levels, postoperative hemoglobin level, conventional/thromboelastography (TEG) coagulation monitoring indices, LOH and AE rate between tTXA and ivTXA groups.

### Study setting and investigators

This trial will be conducted at a single tertiary care teaching hospital. The study settings include the wards and the operating rooms of the orthopedic department (200 beds) at this comprehensive hospital (2500 beds). All the laboratory indices in this study will be tested in the key labs of the teaching hospital.

Participants will be recruited through the outpatient clinic of one investigator, and will be consented by the investigators. All the investigators possess working experience in clinical orthopedic research projects. The surgeries will be conducted by a single team of surgeons who have completed clinical fellowship in spinal surgery.

### Design

This is a prospective, randomized, double-blind, head-to-head, non-inferiority trial that conforms to the Consolidated Standards of Reporting Trials (CONSORT) [15].

The timing of interventions and data collection is detailed in Fig. 1. The flowchart of the study process is detailed in Fig. 2. The Standard Protocol Items: Recommendations for Interventional Trials (SPIRIT) checklist is provided as Additional file 1.

**Fig. 1 Fig1:**
[figure not shown]
Schedule of enrollment, interventions, and assessments

**Fig. 2 Fig2:**
[figure not shown]
Flowchart of the study process

### Participants

Patients aged over 18 years who are classified as American Society of Anesthesiologists (ASA) physical status I–II, diagnosed as having lumbar spinal stenosis/intervertebral disc herniation/spondylolisthesis, requiring lumbar spinal decompression and 3–5 levels of bone graft fusion surgeries will be enrolled in the study after signing a written informed consent.

Patients with past medical history of chronic renal dysfunction (preoperative blood creatinine > 120 mmol/L), liver dysfunction (preoperative blood aspartate aminotransferase (AST) or alanine aminotransferase (ALT) > 50 U/L), coronary artery disease with stent placement, abnormal preoperative coagulation profile (preoperative prothrombin time (PT) elongation > 3 s, activated partial thromboplastin time (APTT) elongation >10 s, platelet counts < 100 × 10^9^/L or > 400 × 10^9^/L, or international normalized ratio (INR) > 1.4), or pre-existing anemia (male < 12 g/dL, female < 11 g/dL), and those who have long-term medications of aspirin and/or other anticoagulants, known allergy to TXA, or religious and/or other beliefs limiting blood transfusion are excluded. Participants who undergo dura mater laceration or unexpected massive bleeding or who receive cell saver application during operation will also be excluded.

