### Intervention

On the morning of the surgery, the appointed nurse will prepare Solutions A, B, and C according to the treatment allocation and the patient body weight (Wt, in kilograms) checked with ID number, with 100 ml Solution A as the loading dose, 100 ml Solution B as the maintenance dose, and 250 ml Solution C as the bolus dose. In the tTXA group, Solution A consists of 100 ml 0.9% normal saline (NS), Solution B consists of 100 ml 0.9% NS, and Solution C consists of 500 mg TXA dissolved in 250 ml 0.9% NS. In the ivTXA group, Solution A consists of 10 mg/kg TXA dissolved in 100 ml 0.9% NS, Solution B consists of 20 × Wt (mg) TXA dissolved in 100 ml 0.9% NS, and Solution C consists of 250 ml 0.9% NS. In both groups, Solution A will be infused as a bolus intravenously 15 min prior to operation initiation, Solution B will be infused at 5 ml/h intravenously from operation initiation until the last suture (i.e., 1 mg/kg/h TXA infusion in the ivTXA group), and Solution C will be applied for topical wound irrigation for 5 min with the waste fluid removed by suction before the wound is closed.

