### Adverse event management and emergency termination of the study

In this study, AEs include, but are not limited to, deep venous thrombosis, myocardial infarction, pulmonary embolism, cerebrovascular disease, impaired liver function, impaired renal function, incisional hematoma/infection, and convulsive seizures. Patients will be closely monitored during the study period. In case of suspicions for the preceding AEs, the study team will break the blind, and patients will be treated appropriately under the instructions of both spine surgeons and internal medicine physicians. All AEs will be diligently recorded and reported in the final manuscript.

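### The only numeric definition of the renal exclusion, creatinine above 120 mmol/L, cannot be met by any patient as printed

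*Protocol article*

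**What the plan says.** In the protocol article, under Participants, the exclusion begins "Patients with past medical history of chronic renal dysfunction" and puts its numeric definition in parentheses: "chronic renal dysfunction (preoperative blood creatinine > 120 mmol/L". The list applies to all candidates before allocation. The same section restricts entry to "American Society of Anesthesiologists (ASA) physical status I–II". No other section gives a renal limit.

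Three other sections show why the criterion is there:

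- **Background** says that high intravenous dose, older age and "preoperative renal dysfunction have been identified as risk factors for developing postoperative TXA-related seizures and strokes".
- **Intervention** gives one arm systemic, weight-based drug: "In the ivTXA group, Solution A consists of 10 mg/kg TXA dissolved in 100 ml 0.9% NS", followed by an infusion until the last suture.
- **Adverse event management and emergency termination of the study** lists among the adverse events "impaired liver function, impaired renal function, incisional hematoma/infection, and convulsive seizures".

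**The concern.** The printed unit gives a creatinine concentration far outside anything a living patient can have. A numeric exclusion that no one can meet does no work, and this one is the only reproducible definition of a safety-related criterion. The article names the patients at higher risk, gives one arm the drug intravenously, and then prints a screen that cannot detect those patients.

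What is at stake is mainly clarity and safety. A reader, auditor or site working from the text cannot apply the limit as written. There is also a formal link to the analysis: under Sample size and statistical analysis, membership of the ITT set depends on meeting all eligibility criteria, so a criterion that cannot be applied leaves the definition of that set partly unclear.

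**Working it through.** There is no derived figure in the article to reproduce. The check is a unit conversion.

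**Inputs**

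- Threshold as printed: 120 mmol/L (Participants).
- Molar mass of creatinine, C4H7N3O, from atomic masses and not given in the article: 4 × 12.011 + 7 × 1.008 + 3 × 14.007 + 15.999 = 113.12 g/mol.
- Assumed range for the most extreme creatinine seen clinically: 1,000 to 5,000 micromol/L. The article gives no such figure, so a wide range is used.
- Assumed blood volume, as a plausibility check only: 3 to 6 L.

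**Step 1. Convert the printed threshold.** Mass concentration = molar concentration × molar mass.

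0.120 mol/L × 113.12 g/mol = 13.57 g/L = 1,357 mg/dL.

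**Step 2. Compare with the assumed ceiling.** 120 mmol/L = 120,000 micromol/L.

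| Assumed highest creatinine (micromol/L) | Printed threshold ÷ ceiling |
|---|---|
| 1,000 | 120 |
| 2,000 | 60 |
| 3,000 | 40 |
| 5,000 | 24 |

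The conclusion is the same across the whole range.

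**Step 3. Check physical plausibility.** At 13.57 g/L, 3 to 6 L of blood would hold 13.57 × 3 = 41 g to 13.57 × 6 = 81 g of creatinine.

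**Step 4. Show the scale of a one-prefix slip.** The same numeral in micromol/L would be 0.01357 g/L, or 1.36 mg/dL, a factor of 1,000 lower. This shows how large the effect of the prefix is. It does not establish which limit the approved protocol contains.

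**Step 5. See what is left of the exclusion.** With the number inoperative, two things in the same section could still exclude a patient with renal disease: the verbal reference to a history of chronic renal dysfunction, and the ASA I–II limit. Neither supplies a laboratory cut-off that two screeners would be bound to apply alike.

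**The case against.** The best case on the other side is that this is an editorial slip with little practical effect. Much of that stands.

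- **The exclusion still has content.** The verbal criterion can be applied without the number, and ASA I–II also restricts entry. A reader might infer that the protocol lets all patients with renal dysfunction in, or that the criterion excludes nobody. The text supports that only for the number, not for the criterion as a whole.
- **Staff probably read the numeral against their own reports.** Study setting and investigators describes one hospital, experienced investigators and the hospital's own laboratories. Someone comparing 120 with a local report may never have noticed the unit. This is an inference, but a reasonable one.
- **The error may be confined to the article.** A lost Greek mu is a familiar typesetting or conversion fault, and the article prints the beta of its power statement with a different letter. The approved protocol is not available to settle the matter.
- **The data checks may be sound.** A reader might infer that the eCRF passes every patient. Data collection and monitoring mentions logic validation but gives no ranges or units and does not say that eligibility is covered.
- **Both arms are concerned.** A reader might take this as a fault of the intravenous arm. The exclusion operates before allocation, so it concerns candidates for both arms; systemic exposure only makes the consequence greatest in that one.

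None of this makes the printed threshold right. It is a complete, legible number and unit in an eligibility rule, and no other section corrects it.

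**Conclusion.** The point holds for the numeric threshold as printed: at about 1,357 mg/dL it lies 24 to 120 times above any assumed clinical ceiling and can never be met. It rests on a chemical constant and on a deliberately wide assumed range for human creatinine, and no value in that range changes the answer. It conflicts with the article's own account of renal dysfunction as a risk factor for harm from the study drug.

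The article does not show that any ineligible patient was enrolled, that the operating protocol has the same fault, or that the ITT set or any estimate is distorted. The sample size and error rates do not depend on this value. It is a clear error of text in a safety-related criterion, worth correcting because the article reports recruitment as ongoing, with practical consequences that are unknown and may be small.

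**What to change.** 1. Reconcile the printed threshold and its unit with the approved protocol and with the unit in which the laboratory reports creatinine, and correct the text. The value is for the investigators to confirm; none is proposed here.
2. Check that any eligibility range in the eCRF uses the reconciled unit.
3. Re-check the eligibility of enrolled patients only if the approved protocol or the eCRF turns out to carry the same error.

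If the slip is confined to the article, the cost is a correction to one threshold and a short check of the eCRF. If it goes further, the added cost is one look-back at the preoperative creatinine of patients already enrolled. The design, sample size and analysis need no change.

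### Exclusions for events during surgery, massive bleeding among them, occur after randomisation and dosing yet remove participants from the ITT set, so the primary analysis selects partly on its own outcome

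*Protocol article*

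**What the plan says.** - **Exclusion rule (Participants).** Directly after the list of baseline exclusion criteria: "Participants who undergo dura mater laceration or unexpected massive bleeding or who receive cell saver application during operation will also be excluded". No volume or other threshold defines massive bleeding.
- **Timing of allocation and first dose (Intervention).** "On the morning of the surgery, the appointed nurse will prepare Solutions A, B, and C according to the treatment allocation", and "Solution A will be infused as a bolus intravenously 15 min prior to operation initiation".
- **Timing of topical drug (Intervention).** "Solution C will be applied for topical wound irrigation for 5 min with the waste fluid removed by suction before the wound is closed". Until then the tTXA arm has received saline alone, while the ivTXA arm has had TXA since before incision.
- **Analysis sets (Sample size and statistical analysis).** The ITT set takes randomised, consented participants who "satisfied all inclusion/exclusion criteria and have completed demographic data will be included in the intention to treat (ITT) analysis set". Next: "All the participants in the ITT set who have completed the perioperative TBL will be included in the per protocol (PP) analysis set". And: "All the analyses on efficacy will be based on the ITT set". The safety set takes everyone randomised who received at least one dose and is used for adverse events.
- **Primary outcome (Primary outcome).** TBL accumulates from the start of the operation to postoperative day 3 (POD3).

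**The concern.** All three events arise during the operation, so they follow both randomisation and the first infusion. Because the ITT definition refers back to the exclusion criteria, they remove people from a set whose name promises that nobody randomised is removed.

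For massive bleeding the problem goes beyond a lost participant. The endpoint counts blood loss from the first incision, so a participant removed for bleeding heavily is removed for the value of the endpoint. Cell-saver use is likely to go with heavy bleeding.

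The removals may also differ by arm, since only ivTXA participants have active drug during the period in which the rule operates. If more heavy bleeders are removed from the tTXA arm, the observed difference and the variance both shrink, and both changes favour a non-inferiority claim. The rule is also a matter of judgement, and the Randomization and concealment section lets a clinician be unblinded during surgery in a suspected emergency, so some exclusions could be decided with the allocation known.

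**Working it through.** **1. Can any planned analysis bring these participants back?**
- ITT: no, it requires all exclusion criteria to be satisfied.
- PP: no, it is a subset of ITT.
- Multiple imputation: nothing in the article extends it to people outside the ITT set.
- Safety set: they stay in it, but it serves adverse events only.

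**2. Inputs for the size.** From Sample size and statistical analysis: ivTXA mean 911 ml, SDs 459 and 460 ml (460 used), margin 195 ml, 88 per arm (70/0.8 = 87.5, rounded up), one-sided 0.025. The true difference is set at the margin, so the tTXA mean is 911 + 195 = 1106 ml. Non-inferiority is declared when the upper t-based limit lies below 195 ml. The plan gives no figure for the effect of the exclusion, so there is none to reproduce. Every cut-off and exclusion rate below is an assumption.

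**3. Sharp cut on TBL.** For normal TBL cut at c, the retained mean is μ − σφ(z)/Φ(z), with z = (c − μ)/σ. At c = 2000 ml:
- tTXA: z = 894/460 = 1.943; mean = 1106 − 460 × 0.0604/0.9740 = 1077.5
- ivTXA: z = 1089/460 = 2.367; mean = 911 − 460 × 0.0242/0.9910 = 899.8
- Difference: 177.7 ml instead of 195 ml.

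Simulation (40,000 trials per setting; normal / lognormal TBL):

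| Cut-off (ml) | Excluded tTXA (%) | Excluded ivTXA (%) | Mean difference (ml) | Type I error (%) |
|---|---|---|---|---|
| none | 0 / 0 | 0 / 0 | 195 / 195 | 2.6 / 2.4 |
| 2500 | 0.1 / 1.3 | 0.0 / 0.9 | 194 / 191 | 2.7 / 2.8 |
| 2000 | 2.6 / 4.6 | 0.9 / 2.9 | 178 / 180 | 4.4 / 4.4 |
| 1800 | 6.6 / 7.8 | 2.7 / 4.8 | 161 / 170 | 7.3 / 6.5 |
| 1500 | 19.6 / 16.8 | 10.0 / 9.9 | 127 / 148 | 19.8 / 16.2 |

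The last row removes (19.6 + 10.0)/2 = 14.8% of participants under normal TBL and (16.8 + 9.9)/2 = 13.4% under lognormal.

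**4. Exclusion on intraoperative loss.** This is closer to the rule. Let intraoperative loss correlate ρ = 0.5 to 0.7 with TBL (assumed) and exclude the highest values, pooled over arms. In SD units the TBL shift is 195/460 = 0.42. Two versions for the arm shift in intraoperative loss, in its own SDs:
- partial: 0.42 × ρ, that is 0.21 to 0.30
- whole (all 195 ml arises during surgery, whose loss has SD ρ × 460): 0.42/ρ, that is 0.85 to 0.61

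| Excluded overall | Type I error, partial | Type I error, whole |
|---|---|---|
| 1% | 2.8–2.9% | 3.4–3.5% |
| 2% | 3.0–3.3% | 4.1–4.5% |
| 5% | 3.4–4.4% | 6.4–7.2% |

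These are for normal TBL (40,000 trials). With lognormal TBL the upper ends are somewhat higher, about 5% at 2% excluded and about 9% at 5%.

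**The case against.** The strongest case accepts the textual chain and contests size and direction.

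- **The sharp cut is the wrong model.** The rule acts on bleeding during the operation, whereas TBL runs to POD3 and includes hidden loss, which the Discussion puts at 39–47% of TBL. This stands, and it is why the second model carries the estimate.
- **A 1500 ml cut is implausible.** It lies (1500 − 1106)/460 = 0.86 SD above the tTXA mean, which hardly describes unexpected massive bleeding in ASA I–II patients screened for anaemia and coagulopathy. This stands. A reader might infer from the 16–20% row that the error rate is inflated six- to eightfold; the article offers nothing to support an exclusion rate near 15%.
- **The direction is not established.** If the events were equally frequent and equally severe in both arms, the mean difference would not be biased, although the variance would still shrink. Exclusions also cost some sample size. This stands: saline alone until closure makes an imbalance plausible, not proven.
- **Dural laceration is not an extreme of blood loss.** This stands. A reader might count all three events as removal of the worst outcomes; nothing in the article links dural tears to TBL or to allocation.
- **The pilot may already omit such cases.** The article does not say. If it does, the simulation truncates twice.
- **The participants do not vanish.** They remain in the safety set and their adverse events are reported. True, but this does not repair the efficacy comparison.

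None of these points restores the excluded participants to any efficacy analysis.

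**Conclusion.** The structural point is firm. As written, participants with these intraoperative events leave every efficacy analysis after randomisation and dosing, and for massive bleeding and associated cell-saver use this is selection on the primary outcome. The likely direction favours non-inferiority, on the assumption that such events are more frequent or more severe in the tTXA arm.

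The size cannot be derived from the article. With a true difference of 195 ml, one-sided 0.025 and assumed exclusion rates, type I error is about 2.5–3.5% if about 1% or fewer are excluded, about 3.5–4.5% at 2% (nearer 3% if only part of the difference arises during surgery) and about 4–7% at 5%. The range therefore starts at practically no inflation. The 16–20% figure is an extreme that needs roughly 15% of participants removed by a sharp cut on TBL. A claim that the trial is certainly biased, or biased to that degree, goes beyond what the document supports. The point still needs correcting, because it decides who counts in the primary test.

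**What to change.** - For the primary analysis, define ITT as all randomised participants analysed as randomised (at minimum, all in whom surgery began), regardless of intraoperative events.
- Collect POD3 haematocrit and TBL in participants who have these events.
- State how re-infused cell-saver volume enters TBL. The Secondary outcomes section adds only allogeneic volume, so the endpoint is at present undefined for these participants.
- Use the set without these events only as a supportive analysis, and report the number of each event by arm.

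This changes analysis and data handling, not clinical care. The costs are a revised definition, a stated rule for cell-saver volume, POD3 follow-up of these participants, and a somewhat larger TBL variance from the retained heavy bleeders. The article describes the trial as still recruiting, so on that status the change could be made before analysis.
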